## Abstract

**Background:**

Acute pharyngitis is one of the most frequent consultations to the general practitioner and in most of the cases an antibiotic is prescribed in primary care in Spain. Bacterial etiology, mainly by group A beta-hemolytic streptococcus (GABHS), accounts for 10-20% of all these infections in adults. The purpose of this study is to assess the impact of rapid antigen detection testing (RADT) to identify GABHS in acute pharyngitis on the utilization of antibiotics in primary care.

**Methods/design:**

Multicentric randomized controlled trial in which antibiotic prescription between two groups of patients with acute pharyngitis will be compared. The trial will include two arms, a control and an intervention group in which RADT will be performed. The primary outcome measure will be the proportion of inappropriate antibiotic prescription in each group. Two hundred seventy-six patients are required to detect a reduction in antibiotic prescription from 85% in the control group to 75% in the intervention group with a power of 90% and a level of significance of 5%. Secondary outcome measures will be specific antibiotic treatment, antibiotic resistance rates, secondary effects, days without working, medical visits during the first month and patient satisfaction.

**Discussion:**

The implementation of RADT would allow a more rational use of antibiotics and would prevent adverse effects of antibiotics, emergence of antibiotic resistance and the growth of inefficient health expenses.

**Trial registration:**

ISRCTN23587778

Over the last years, low-cost and rapid immunological techniques targeting the detection of GABHS antigens have been developed for use in the clinical setting. Their high specificity (>95) make the probability of obtaining false positive results very low [11-13]. A recent paper published in Greece shows that the use of these tests can reduce the prescription of antibiotics in pharyngotonsillitis in children [14]. However, very few studies have been carried out to know the impact of RADT on the pattern of how general practitioners prescribe antibiotics for patients with pharyngotonsillitis in adults.

## Methods/Design

### Objectives

The main objective of this investigation is to assess the impact of the RADT in adults with acute pharyngitis on the percentage of antibiotics prescribed by general practitioners

The secondary objectives are:

a. To describe the antibiotics prescribed.

b. To describe GABHS resistance to the antibiotics prescribed.

c. To assess clinical recurrence within the first month.

### Design

Multicenter randomized clinical trial designed to compare antibiotic prescription in patients with acute pharyngitis in two groups of physicians, one with the use of RADT and the other without these tests.

### Setting

The trial will be conducted in Primary Health Care Centers in Catalonia (Spain) in which the clinical history records are accessed electronically.

### Participants

#### Study population

Eligible patients will be consecutively selected by general practitioners. All patients who agree to participate will be asked to provide written informed consent and an informative sheet of the study.

#### Inclusion criteria

1. Men and women aged 14 to 60 years.

2. More than one symptom of acute pharyngitis, such as fever, sore throat, tonsillar exudates, tender cervical nodes and/or absence of cough.

#### Exclusion criteria

1. Patients who do not consent to participate.

2. Patients younger than 14 or older than 60 years of age.

3. More than five episodes of pharyngitis over the last year.

4. Immunosuppressed condition, such as active neoplasm, acquired immunodeficiency syndrome or reception of chemotherapy, radiotherapy, corticosteroids and/or immunosuppressive therapy.

5. Heart valve disease.

6. Rheumatic fever.

7. Episode of pharyngitis treated with antibiotics in the previous fifteen days.

8. Pharyngitis of gonococcal etiology.

9. Tonsillectomy.

### Outcome measures

Primary outcome: proportion of inappropriate antibiotic prescription, use of antibiotic treatment, use of RADT, RADT result, and culture result.

#### Secondary outcomes

- Intervention arm only: RADT result.

- Both intervention and control groups:

**a**. Age, sex, clinical symptoms (fever, sore throat, tender cervical nodes, absence of cough), specific antibiotic treatment, culture result, antibiotic resistance, side effects, days without working, change of antibiotic, and medical visits within the first month.

**b**. Patient satisfaction. Patients will be required to score the degree of satisfaction, from 0 (no satisfaction at all) to 10 (very satisfied), for the following items: ease of obtaining a visit the day the patient wants, duration of the visit, doctor clinical ability, doctor kindness, doctor predisposition to listen, the way the problem is solved, the feeling of being in "good hands", and overall satisfaction with the doctor. Patients will be asked if they have been attended by their usual doctor or not and if they would recommend the attending doctor to a friend or relative. The open questions include: What is the most satisfying aspect of the visit? What is the worst aspect of the visit? Would you like to make any comment on anything else?

### Ascertainment of visits

#### Baseline data collection

The baseline questionnaire at the clinical practice will include age, sex, clinical symptoms, specific antibiotic treatment, use of RADT and RADT result.

#### Follow-up data collection

• 48-72 h data collection by means of a phone call that will include side effects, days without working, and change of antibiotic or not.

• Three-week data collection: The questionnaire will include the number of visits, if there has been any complication, culture result and antibiotic resistance to GABHS if the culture is positive.

• The satisfaction interview will be given one month after the baseline visit.

### Sample size

Two hundred seventy-six patients are required in each arm to detect a reduction of 10% in antibiotic prescription from 85% in the control group to 75% in the intervention group, assuming a rate of 85% of prescription in the control group, allowing 10% for losses in the follow-up visits, with a power of 90% and a level of significance of 5% (2-sided) and performance values of the RADT given by the manufacturer.

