### Randomization

The unit of randomization will be the primary health care center, which will be allocated to the control or intervention group by a random sequence generated by a computer program. This unit of randomization will be taken into account in order to minimize contamination between these two groups. It may not be appropriate to randomize individuals since patients who attend the same primary health care center may be treated in the same way. Patients who meet the inclusion criteria will be consecutively selected by the participating physicians and allocated to the treatment group corresponding to the center.

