## Discussion

This article presents a detailed description of a randomized clinical trial designed to explore the impact of RADT on antibiotic prescribing in acute pharyngitis in adults. The trial proposed is sufficiently powered and, to the best of our knowledge, the first to allow conclusions on the effect of RADTs in adults with pharyngitis. Pharyngotonsillitis is a very prevalent disease and is one of the most frequent causes of medical visits in primary care. Many patients in our country visit the physician in search of antibiotic prescription since they believe that this is the treatment of choice, particularly among patients with multiple disease recurrence. In other cases, patients seek home remedies or go directly to the pharmacy to obtain medications to alleviate the sore throat that accompanies pharyngitis. Primary care physicians are aware that when the patients visit they wish to receive effective treatment with medications which rapidly alleviate the accompanying symptomatology and, in many cases, what they want is treatment with an antibiotic. This is probably the main reason why physicians in our country mainly prescribe these medications together with the fact that it is clinically difficult to distinguish streptococcal from viral etiology. We believe that this clinical trial will be of great use to know whether the RADT are truly effective in reducing the percentage of antibiotic prescription in our setting.

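### The sample size treats patients as individually randomised, so the stated 90% power does not apply to a trial that randomises health centres

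*Protocol article*

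**What the plan says.** The Randomization section sets the design: "The unit of randomization will be the primary health care center". Part of its reasoning is that "It may not be appropriate to randomize individuals since patients who attend the same primary health care center may be treated in the same way". The Intervention section also says that centres are randomised to the arms.

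The Sample size section says "Two hundred seventy-six patients are required in each arm to detect a reduction of 10% in antibiotic prescription". Its inputs are prescription rates of 85% and 75%, 10% for losses, 90% power, two-sided 5% significance and the manufacturer's performance values for the test. It names no intracluster correlation, design effect, number of centres or patients per centre.

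The Analysis section plans chi-square tests on the percentage of prescriptions and states no adjustment for centre. The Discussion concludes: "The trial proposed is sufficiently powered".

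**The concern.** When whole centres are allocated, patients in one centre are not independent observations, and the effective sample size is the number of patients divided by the design effect. Here the outcome is the doctor's decision to prescribe, and patients in a centre share doctors and local prescribing habits, so some correlation within centres is to be expected. The protocol concedes this when it explains why centres are randomised. That explanation is a reason to inflate the sample size, yet the inputs listed are those of an individually randomised trial.

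The power for the main comparison is at stake. If the analysis respects the clustering, the trial could miss its own 10-point target with substantial probability, and a null result could be misread as showing that the rapid test does not change prescribing. If the analysis ignores the clustering, the type I error rate is no longer 5%.

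**Working it through.** **Inputs from the Sample size section.** p1 = 0.85, p2 = 0.75, mean 0.80; two-sided 5% (z = 1.96); 90% power (z = 1.2816); 10% losses; 276 per arm.

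**Step 1. Try to reproduce 276 without clustering.** The usual two-proportion formula is

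n = [z_alpha × √(2 × 0.80 × 0.20) + z_power × √(0.85 × 0.15 + 0.75 × 0.25)]² / 0.10²

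= [1.96 × 0.5657 + 1.2816 × 0.5612]² / 0.01 = 334.2, so 335 per arm.

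With 10% losses, 335 / 0.9 = 372.2, so 373. A continuity correction gives 354, or 394 after losses. The unpooled and arcsine versions give 331 and 332 before losses. None yields 276.

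The figure is close to what 80% power would need: 250 per arm, and 250 / 0.9 = 277.8, so 278.

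Since 276 is smaller than the unclustered requirement, it cannot contain a design effect above 1.

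**Step 2. Power of the stated size without clustering.** The same formula, solved for power, is

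power = Φ{[0.10 × √n − 1.96 × 0.5657] / 0.5612}

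- n = 276: 83.8%.
- n = 248 (276 × 0.9 = 248.4): 79.7%.

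**Step 3. Add clustering.** The design effect is DE = 1 + (m − 1) × ICC, and n is replaced by n / DE. The protocol gives neither m (evaluable patients per centre) nor the ICC, so both are assumed over a range.

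Example with m = 20 and ICC 0.05: DE = 1 + 19 × 0.05 = 1.95; 248 / 1.95 = 127.2; power = Φ{[0.10 × 11.277 − 1.1088] / 0.5612} = Φ(0.034) = 51%.

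Power from 248 evaluable per arm, with the value for all 276 in brackets:

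| m | ICC 0.01 | ICC 0.02 | ICC 0.05 | ICC 0.10 |
|---|---|---|---|---|
| 5 | 78% (82%) | 77% (81%) | 72% (77%) | 65% (70%) |
| 10 | 76% (81%) | 73% (77%) | 64% (68%) | 52% (57%) |
| 20 | 73% (77%) | 66% (71%) | 51% (56%) | 37% (41%) |
| 30 | 69% (74%) | 60% (65%) | 43% (47%) | 29% (32%) |

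These are normal approximations. A small number of centres would lower the values further.

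**Step 4. Size needed for the stated 90% power.** Multiply 335 by DE and divide by 0.9. For ICC 0.01 to 0.10 this gives 406 to 708 per arm at m = 10, and 443 to 1,080 at m = 20.

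**Step 5. If clustering is ignored in the test.** The true two-sided error of a nominal 5% test is about 2 × [1 − Φ(1.96 / √DE)]: 6% at DE 1.09, 10% at 1.45 and 16% at 1.95.

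**The case against.** Five points can be made in the plan's defence.

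- **The article is condensed.** The ICC and number of centres could stand in a fuller protocol, and silence alone would be weak evidence. But a figure below the unclustered requirement cannot include an allowance for clustering, whatever a fuller document says.
- **Not all of the shortfall from 90% is due to clustering.** This stands. The figure of 276 does not match 90% power even for individual randomisation, which is a separate fault. The fair starting point for the clustering loss is 79.7% (248 evaluable) or 83.8% (all 276). At m = 10 and ICC 0.02, for example, clustering costs about 7 points, from 80% to 73%.
- **248 may be too few.** The allowance is worded "allowing 10% for losses in the follow-up visits", while antibiotic treatment is recorded in the baseline questionnaire, so losses need not remove prescription data. Against that, the Analysis section places the primary end point at baseline and at three weeks. Using all 276 raises power by about 3 to 5 points and does not change the conclusion.
- **Power near one half depends on the assumptions.** This also stands. It arises around m = 20 with ICC 0.05, or m = 10 with ICC 0.10. With five patients per centre and ICC 0.01 to 0.02 the clustering loss is only 1 to 3 points.
- **The protocol says that the unit of randomisation will be taken into account.** That sentence in the Randomization section concerns contamination between arms, not sample size.

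**Conclusion.** The concern holds. The trial randomises centres, its sample size is that of an individually randomised trial, and the stated 90% power is not a property of the design. That conclusion does not depend on any assumed ICC: it follows from 276 being less than 335.

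The size of the loss does depend on assumptions. For ICC 0.01 to 0.10, with 248 evaluable per arm and an analysis that allows for clustering, power runs from 76% down to 52% with 10 patients per centre, and from 73% down to 37% with 20. At a moderate correlation the trial may have close to even odds of detecting its own target effect. As written, the Discussion's claim of sufficient power should not stand.

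**What to change.** In the Sample size section, state the planned number of centres per arm and the mean number of patients per centre. Assume an ICC, give its basis and show a range such as 0.01 to 0.10. Apply 1 + (m − 1) × ICC, and restate the power or the detectable difference at the fixed 276 per arm, for an analysis that allows for clustering. Start from the unclustered 80% or 84% rather than 90%, so that the two sources of shortfall stay distinct. In the Discussion, withdraw the claim of sufficient power or qualify it to match.

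The cost is one rewritten paragraph, a changed sentence in the Discussion and a less favourable stated power. The restatement needs no added patients. Keeping 90% as the target would instead require a larger trial, of the order shown in step 4 of the working.

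### 276 patients per arm with 10% losses gives about 80% power for 85% versus 75%, not the stated 90%, even before clustering

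*Protocol article*

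**What the plan says.** The Sample size section of the protocol article fixes every input to the calculation:

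- Size: "Two hundred seventy-six patients are required in each arm".
- Effect: a fall in antibiotic prescription "from 85% in the control group to 75% in the intervention group".
- Losses (already inside the 276), power and test level: "allowing 10% for losses in the follow-up visits, with a power of 90% and a level of significance of 5% (2-sided").

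The abstract (Methods/design) repeats 276, the same two rates and the same power ("with a power of 90% and a level of significance of 5"%), but does not say that 276 is per arm. The Analysis section plans chi-square tests to compare prescription between the arms. The Discussion builds on the calculation: "The trial proposed is sufficiently powered".

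**The concern.** For rates of 85% and 75%, 276 per arm including losses is too few for 90% power at a two-sided 5% level, and it is close to what 80% power would require. If so, the stated power does not follow from the inputs beside it.

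The stated power is the figure a reader uses to judge a non-significant result. If the true type II error is up to twice the 10% implied, a failure to show a 10-point reduction says less about the rapid test than the protocol suggests. The sponsor would also be recruiting to a target well below the one its own assumptions call for.

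**Working it through.** **Inputs** (Sample size section): p1 = 0.85, p2 = 0.75, difference 0.10, two-sided alpha 0.05 (z = 1.960), power 0.90 (z = 1.2816), losses 10%, equal arms. The mean rate is 0.80. Clustering is set aside throughout, which favours the plan.

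**Formula** (pooled two-proportion comparison, matching an uncorrected chi-square test):

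n per arm = [z_alpha × √(2 × p̄ × (1 − p̄)) + z_beta × √(p1(1 − p1) + p2(1 − p2))]² / (p1 − p2)²

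Here 2 × 0.80 × 0.20 = 0.320 and 0.85 × 0.15 + 0.75 × 0.25 = 0.315, so the square roots are 0.5657 and 0.5612.

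**Step 1: attempt to reproduce 276 at the stated 90% power.**
n = (1.960 × 0.5657 + 1.2816 × 0.5612)² / 0.01 = (1.1087 + 0.7193)² / 0.01 = 334.2, rounded up to 335. With 10% losses, 335/0.9 = 372.2, rounded up to 373.

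| Formula, 90% power, two-sided 5% | Evaluable per arm | With 10% losses |
|---|---|---|
| Pooled | 335 | 373 |
| Unpooled | 331 | 368 |
| Continuity-corrected | 354 | 394 |

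None is near 276. Against the pooled result, 276 is short by 1 − 276/373 = 26%.

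**Step 2: find what does give 276.** At 80% power (z = 0.8416) the pooled formula gives (1.1087 + 0.4724)² / 0.01 = 250. Adding losses gives 250/0.9 = 278, or 250 × 1.1 = 275. The unpooled formula gives 247.2, rounded up to 248, and 248/0.9 = 275.6, which rounds up to 276 exactly. That the authors used 80% is an inference, but the mismatch with 90% does not depend on it.

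**Step 3: power at the stated size.** 276 × 0.9 = 248.4, so 248 evaluable per arm.

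Power = Φ[(0.10 × √n − 1.1087) / 0.5612]

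| Evaluable per arm | z | Power | Exact enumeration of the uncorrected chi-square test |
|---|---|---|---|
| 248 (10% lost) | 0.830 | 79.7% | 79.9% |
| 276 (none lost) | 0.985 | 83.8% | 84.0% |

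With a continuity correction the exact power falls to 76.8% and 81.4%.

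**Step 4: the effect for which 90% power would hold.** Solving the power formula for p2 with p1 = 0.85 and 248 per arm gives p2 = 73.2%, a difference of 11.8 points. With 276 per arm and no losses, p2 = 73.9%, a difference of 11.1 points.

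**Step 5: other readings.**

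- One-sided 5% at 90% power needs 273 before losses, close to 276. It contradicts both the stated two-sided level and the stated loss allowance.
- Two-sided 80% power with continuity correction needs 270 before losses. It contradicts the stated power and the loss allowance.
- One-sided 5%, 85% power, continuity-corrected, with losses gives 277. It contradicts the stated sidedness and power.
- Taking 276 as the total, as the abstract could be read, leaves 138 per arm (124 after losses) and 55% (50%) power.
- Taking 10% as a relative reduction (85% to 76.5%) raises the need to 451 evaluable per arm and contradicts the stated 75%.

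**The case against.** The strongest objection concerns losses. The allowance is for follow-up visits, whereas antibiotic treatment is recorded on the baseline questionnaire, so dropout need not remove anyone from the prescription comparison. On that reading the power is 83.8%, and the type II error about 16% rather than 20%. This is a fair limit on the size of the error. It does not remove it, because even with no losses the power is 6 points short of 90%. Some loss may in any case apply, since the Analysis section places the primary end point at baseline and at three weeks and includes the culture result.

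A second objection is that restating the power as 80% for individually randomised patients still does not describe a trial that randomises centres. That stands. The document gives no intra-centre correlation, so the true power cannot be derived from it. Purely as an assumption, design effects of 1.1, 1.2 and 1.5 on 248 evaluable per arm would give about 76%, 72% and 62%. The point made here does not rest on those figures.

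The section also cites the manufacturer's performance values for the test, which are not given. They may lie behind the assumed 75%, but they cannot alter a comparison already fixed at 85% versus 75%.

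Finally, how a null result would be read is a prediction, since the document does not say. The arithmetic error does not depend on it.

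**Conclusion.** The concern holds. The stated 90% power is wrong for the stated inputs: no reading that keeps the two rates, the two-sided 5% level and 276 per arm reaches it. Power is about 80% under the protocol's own 10% loss allowance and at most about 84% with no losses, so the type II error is 16% to 20% instead of 10%. The inputs as written call for about 373 per arm (368 with the unpooled formula).

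These figures assume an uncorrected chi-square test, equal arms and independent patients. The last assumption flatters a centre-randomised design, so they are upper values if responses are positively correlated within centres. Because this is a contradiction among figures printed in one sentence, neither an unseen analysis plan nor the condensing of a journal article explains it. It must be corrected.

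**What to change.** Keep 276 per arm and correct the claim:

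1. In the Sample size section, state that 276 per arm, with 10% losses allowed for, gives about 80% power to detect 85% versus 75% at two-sided 5%, calculated for individually randomised patients and before any design effect.
2. Make the same correction in the abstract, and say there that 276 is the number per arm.
3. Remove the statement in the Discussion that the trial is sufficiently powered.

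This costs two corrected sentences and one deleted phrase. No patients are added, and the stated power becomes less favourable.

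If the sponsor prefers to keep 90%, there are two honest routes. One is to attach it to a difference of about 12 points (85% to 73.2%), which also costs only wording. The other is to raise the target to about 373 per arm before any design effect, which adds 373 − 276 = 97 patients per arm. Neither route supplies a power figure for the centre-randomised design; that needs an assumed intra-centre correlation, which this document does not state.

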### Randomization

The unit of randomization will be the primary health care center, which will be allocated to the control or intervention group by a random sequence generated by a computer program. This unit of randomization will be taken into account in order to minimize contamination between these two groups. It may not be appropriate to randomize individuals since patients who attend the same primary health care center may be treated in the same way. Patients who meet the inclusion criteria will be consecutively selected by the participating physicians and allocated to the treatment group corresponding to the center.

